## **Subjects**

Target population Pregnant women with prenatal care in the health care centres of the ASSIR from Catalonia

Inclusion criteria. Older pregnant women with prenatal care in the centres study, with childbirth in the reference hospitals, who wish to participate in the study and want to fill in the birth plan

Exclusion criteria. Illiteracy, language barrier, drug addiction, alcoholism, grade 2, 3 and 4 heart disease, severe associated maternal pathology, type I-II diabetes, uterine malformation, diagnosed foetal malformation, threatened preterm birth, twin or multiple pregnancy, cervical incompetence, previous perinatal death, intrauterine growth retardation, placenta previa, isoimmunization, mild-severe preeclampsia, premature rupture of membranes, maternal infection.

Sample size. The sample calculation has been made based on the main variable of the study “presentation of birth plans”. Based on the descriptive pilot study (n = 211 pregnant women), 48% of the women who receive the usual advice presented the

birth plan to the hospital. It is estimated that this prevalence may be higher in women who receive counselling, around 68%. In this study, a randomized, multicentre and parallel experimental design in clusters is proposed (4 ASSIRs participate). Applying an alpha error of 5%, a beta error of 20% and taking into account the influence of the clusters in the analysis, a total of 133 are required in the control group and 133 in the intervention group. 15% loss to follow-up has been estimated. The calculation has been carried out using the macros of SPSS V22. An interim analysis will be performed to assess whether the sample size needs to be recalculated so that there is sufficient power for the subgroup analysis.

Sampling technique. In the random assignment of ASSIR, the characteristics of the reference hospitals will be taken into account, since they have different levels of care. Thus, two ASSIRs will be assigned to the intervention group and two to the control. For this assignment, the Epidat 4.1 program will be used. This type of assignment has been chosen to avoid contamination among midwives who will or will not receive specific training on birth plan counselling based on shared decision making.

The sampling technique of pregnant women within each ASSIR will be consecutive and proportional to the number of first visits (see table 1).

Table 1. Proportional sampling according to the number of first ASSIR visits

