### Outcome variables

#### Variables related to the birth plan

- Presentation of the birth plan to the hospital: yes, no.
- Reasons of non-presentation to the birth plan: I did not think it was necessary, I forgot, the professionals who attended me did not ask me, others.
- Usefulness of completing the birth plan in decision-making on aspects of childbirth. On an interval scale from 1 to 5. 0 is not useful at all and 5 is very useful.
- Sufficient information received during the pregnancy about the birth: yes, no
- Use of the birth plan in the next pregnancy: yes, no
- Common preferences on aspects of childbirth expressed in the birth plans: yes, no.
- Companion.
- Physical space: unique space, light graduation.
- Comfort measures and support for childbirth: listen to music, birthing ball.
- Drink fluids during labour.
- Foetal monitoring: continuous, intermittent.
- Freedom of movement.
- Pain relief methods: try labour without anaesthesia, epidural, relaxation techniques, breathing techniques, massage, others non-pharmacological

alternatives methods.

- Birth: directed pushing, spontaneous pushing, choose birthing position, use of the mirror for the birth,
- Baby: Early skin to skin in the delivery room, delayed clamping of the umbilical cord, breastfeeding delivery room, I do not want to breastfeed, consult my opinion before giving food to the baby
- Change of preferences regarding aspects of childbirth.

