### **Analysis.**

A descriptive analysis of all variables will be carried out. The categorial ones with frequencies and percentages; the quantitative ones with mean and standard deviation and if they do not comply with a normal distribution, the median, minimum, and maximum will be observed. The statistical software package SPSS 22.0 will be used. Homogeneity tests between the groups will be performed for the main sociodemographic variables to analyse the comparability of the groups. Hypothesis contrast tests, Chi-square test and Student's t test will be performed. A statistical significance level of 5% will be used. Confidence level will be settled on 95%. A multivariate analysis, relative risks and number of subjects will be calculated with a confidence interval of 95%.

**Bibliographic search.** The databases consulted for the search were MEDLINE; Cochrane; EBSCO; CINAHL and CUIDEN from 2000 to 2016 Keywords: birth plans, assessment, midwife, satisfaction, decision making.

**Ethical aspects.** The principles of the Declaration of Helsinki  will be considered and the necessary precautions will be taken to minimize the possible repercussions on pregnant women during the investigation according to the recommendations of the Belmont report.  Authorization will be requested from the Committee on Clinical research ethics of the Jordi Gol i Gorina Foundation for the ASSIR of the Catalan Institute of Health. The information sheet and informed consent is common for participants in the control and intervention group. Throughout the process, the confidentiality of the data will be guaranteed according to Organic Law 15/1999, on the protection of confidential data .

**Difficulties and limitations.** Women can also access birth plan information through other pregnant women or other means such as the internet that could modify decisions regarding it. To avoid contamination among midwives in the counselling

activity, a randomization of ASSIR has been chosen. The possible losses that may be due to a change in the risk of gestation after 29 weeks that limit following the completed birth plan and/or require a childbirth in a hospital other than that of reference. In situations where neonatal death occurs, the degree of satisfaction will not be evaluated.

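### Eligibility and expected losses depend on events after allocation (risk change, birth in another hospital), although plan presentation can usually still be asked

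*Protocol*

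**What the plan says.** **Eligibility** (Protocol, Subjects). The inclusion criteria require prenatal care in a study centre "with childbirth in the reference hospitals, who wish to participate in the study and want to fill in the birth plan". The exclusion list contains preeclampsia, premature rupture of membranes, threatened preterm birth and growth retardation, and does not say up to what time they apply.

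**Timing** (Protocol, Data collection procedure and Intervention). Midwives recruit and take consent at the 24-28 week visit. The ASSIR is the randomised unit, so a woman's arm is settled before she enters. Counselling follows at 29-33 weeks.

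**Losses** (Protocol, Difficulties and limitations). The text speaks of "possible losses that may be due to a change in the risk of gestation after 29 weeks" that hinder following the plan and/or "require a childbirth in a hospital other than that of reference". Subjects, Sample size, allows 15% for loss to follow-up.

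**Outcome** (Protocol, Variables related to the birth plan; Data collection and tools). The item is "Presentation of the birth plan to the hospital: yes, no". The woman answers it herself on a short questionnaire, which also asks for the reason if the answer is no. The ASSIR midwife hands it out at the postpartum visit, up to six weeks after the birth.

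**Size of trial** (Protocol, Subjects). "The sample calculation has been made based on the main variable of the study", which is plan presentation, with 48% expected under usual advice, 68% under the intervention, and 133 women per group.

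**The concern.** At 24-28 weeks nobody knows for certain where a woman will give birth, or whether one of the listed complications will develop. A criterion that can be checked only at delivery, together with a text that counts later risk changes and transfers as losses, invites midwives to treat such women as no longer in the study.

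The reason given for these losses is that the plan cannot be followed or that the birth takes place elsewhere. It is not that the woman cannot be contacted. Neither reason prevents her from saying whether she presented the plan.

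If these women leave the denominator, the presentation rate is conditioned on something that happened after allocation. They may well be less likely to present a plan. Unequal removal would then shift the comparison between arms. The protocol itself contains a reason why removal could be unequal: Subjects, Sampling technique, says the reference hospitals differ in the level of care they provide, so the same complication might mean a transfer from one and not from another. With two ASSIRs per arm, taking hospital characteristics into account at allocation helps but cannot guarantee balance.

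**Working it through.** **1. The passages side by side**

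| Element | When it is known | Can the outcome still be asked? |
|---|---|---|
| Consent and enrolment | 24-28 weeks | - |
| Risk change named as a loss | after 29 weeks | yes, if she attends or is contacted postpartum |
| Birth in another hospital | at delivery | yes, under the same condition |
| Neonatal death | after delivery | yes; only satisfaction is dropped |

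The last row shows that the protocol can set a rule for a single outcome. It sets none for risk change or transfer.

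**2. The plan's own figure**

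Inputs from Subjects, Sample size: "48% of the women who receive the usual advice presented the" plan; for the intervention, "It is estimated that this prevalence may be higher in women who receive counselling, around 68"%; and "Applying an alpha error of 5%, a beta error of 20% and taking into account the influence of the clusters in the analysis". A two-sided test is assumed. With pooled variance and no continuity correction:

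n = [1.96·√(2·0.58·0.42) + 0.842·√(0.48·0.52 + 0.68·0.32)]² / 0.20², which gives 95 per arm.

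After 15% loss: 95/0.85 = 112. With continuity correction the figures are 105 and 124. Reaching 133 requires a design effect of 133·0.85/95 = 1.19 (or 1.08 with continuity correction). The protocol states no design effect, so 133 can be neither confirmed nor refuted. The present point does not depend on it.

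**3. False difference if such women are dropped, with no true effect**

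Let the true rate among all enrolled women be 48% in both arms. Let L be the share dropped and q their presentation rate. The rate among those retained is (0.48 - L·q)/(1 - L). The values of L and q are assumptions.

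| L in the two arms | q | Retained rates | False difference |
|---|---|---|---|
| 15% / 15% | 0% | 56.5% / 56.5% | 0 |
| 15% / 15% | 24% | 52.2% / 52.2% | 0 |
| 10% / 20% | 24% | 0.456/0.90 = 50.7%; 0.432/0.80 = 54.0% | 3.3 points |
| 10% / 20% | 0% | 0.48/0.90 = 53.3%; 0.48/0.80 = 60.0% | 6.7 points |

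The sign reverses if the larger loss falls in the other arm.

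**4. Dilution if such women are kept**

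Assume that 15% per arm have such an event and present equally in both arms, at any rate from 0% to 48%. Assume also that 48% and 68% describe the remaining women; the protocol does not say whether the pilot rate included women with such events. The difference among all enrolled is then 0.85·(0.68 - 0.48) = 17 points.

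That needs 133 to 135 analysed women per arm before any design effect. Applying the 1.19 from step 2 gives 133·1.19 = 158.3 and 135·1.19 = 160.7, or 159 to 161 per arm.

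**The case against.** Several points stand against a stronger reading.

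- **No exclusion is stated.** A reader might infer that the protocol removes these women from the analysis or breaks an intention-to-treat commitment. It does neither in words. It speaks of possible losses in a limitations paragraph, never mentions intention to treat, and may leave the analysis set to an SAP that is not shown. The conflict is with good practice, not with another passage.
- **The criteria can be read more kindly.** Recruitment is at 24-28 weeks, so eligibility may be meant to be checked then, with the reference hospital as the planned place of birth. This is plausible, but the text does not say so.
- **Some women will be truly missing.** The Background section describes ASSIR midwives as following women at low and medium risk. A woman whose risk rises may leave that care and not attend the postpartum visit. The outcome is therefore usually, but not always, obtainable.
- **Counselling as the cause of unequal loss.** A reader might infer that counselling changes where women give birth. The paragraph describes births that have to take place elsewhere because of risk, not by choice, so the documents do not support this. Differences between hospitals are the better-supported route.
- **A larger bias figure.** Removing 15% from one arm only, all of them non-presenters, would give 0.48/0.85 = 56.5%, or 8.5 points. That is an extreme bound. It also assigns the whole loss allowance to these events, which the protocol does not do.

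The SAP argument does not settle the matter. Eligibility and data collection belong to the protocol, and if no questionnaire is given, no analysis plan can recover the answer.

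**Conclusion.** The point holds in a limited form. Taken literally, the inclusion criterion, the undated exclusions and the description of losses condition the main outcome on events after allocation, for women whose answer could usually still be obtained.

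The size is uncertain, because the documents give no rate of risk change or transfer by arm. Under the assumed 10% against 20% imbalance, the false difference is one sixth (3.3/20) to one third (6.7/20) of the target effect. With equal losses there is none under the null, although dropping these women could still overstate a real effect (20 points among those retained, 17 among all enrolled, on the step 4 assumptions). This should be corrected, but it does not show that the planned comparison is biased.

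**What to change.** 1. Reword the inclusion criterion to planned birth in the reference hospital, as known at 24-28 weeks, and state that the exclusions apply at enrolment only.
2. Ask the presentation question of every enrolled woman who can be reached, whatever her risk change or hospital. Because women are told to bring the plan to the reference hospital while the outcome item names only the hospital, state in advance which hospital the answer refers to.
3. Analyse all women with an answer by their ASSIR's arm, and count as lost only those whose answer cannot be obtained.
4. Report risk changes and transfers by arm, and keep reference-hospital births as a sensitivity analysis.

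Cost: a protocol amendment and an existing questionnaire given to more women, with no new instrument. Women who have left ASSIR care may need to be traced, and some will still be missing. Power should be rechecked for the diluted effect, with the design effect stated.

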## Timeline

|                                                                                                                                          | September 2016 | October-December 2016 | February- April 2017 | March- June 2017 | May 2017 | June-July 2017 | September 2017 | October 2017 | November 2017 -February 2019 |
|------------------------------------------------------------------------------------------------------------------------------------------|----------------|-----------------------|----------------------|------------------|----------|----------------|----------------|--------------|------------------------------|
| Bibliographic review                                                                                                                     |                |                       |                      |                  |          |                |                |              |                              |
| Requests and authorizations                                                                                                              |                |                       |                      |                  |          |                |                |              |                              |
| Preparation of a dossier for the midwives of the intervention group on the scientific evidence on aspects that appear in the birth plans |                |                       |                      |                  |          |                |                |              |                              |
| Preparation of the provisional leaflet                                                                                                   |                |                       |                      |                  |          |                |                |              |                              |
| Leaflet consensus meetings                                                                                                               |                |                       |                      |                  |          |                |                |              |                              |
| Final design of the leaflet                                                                                                              |                |                       |                      |                  |          |                |                |              |                              |
| Training workshop for midwives of the intervention group                                                                                 |                |                       |                      |                  |          |                |                |              |                              |
| Test pilot                                                                                                                               |                |                       |                      |                  |          |                |                |              |                              |
| Data Collect                                                                                                                             |                |                       |                      |                  |          |                |                |              |                              |

## Annexes

### Annex 1. Protocol study flow chart

[figure not shown]
